**Methods:**

This is a randomized controlled trial in female breast cancer patients undergoing mastectomy and flap fixation using sutures with or without sentinel lymph node biopsy (SLNB). Patients will be eligible for inclusion if they are older than 18 years, have an indication for mastectomy with or without sentinel procedure. Exclusion criteria are modified radical mastectomy, direct breast reconstruction, previous history of radiation therapy of the unilateral breast, breast conserving therapy and inability to give informed consent. A total of 250 patients will be randomly allocated to one of two groups: mastectomy combined with flap fixation and closed-suction drainage or mastectomy combined with flap fixation without drainage. Follow-up will be conducted up to six months postoperatively. The primary outcome is the proportion of patients undergoing one or more seroma aspirations. Secondary outcome measures consist of the number of invasive interventions, surgical site infection, quality of life measured using the SF-12 Health Survey, cosmesis, pain and number of additional outpatient department visits.

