#### Secondary objectives

Assess whether patients with or without drainage after mastectomy experience more pain, experience different quality of life, undergo more invasive interventions related to seroma, develop more surgical site infections or require more unplanned visits to the hospital. Self-assessed cosmesis will also be evaluated.

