### Mastectomy with low vacuum drainage

In the group with closed suction drainage, one low vacuum drain will be placed in the mastectomy gutter, lateral to the pectoral muscle before flap fixation is performed. The drain is connected to a low suction drain bottle. Drain output will be recorded daily. Drain removal will be performed once daily output is below 50 mL or after a maximum of 48 h, irrespective of drain output.

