#### Secondary outcome measures

Assess:
Number of invasive interventions related to seroma or wound healing defined as: every aspiration of clinically significant seroma, incision and drainage of abscess or infected seroma and/or operative debridement of the wound.Surgical site infection (SSI) rate, defined as redness, pain, heat or swelling at the site of the incision or by the drainage of pus. Infection rate will be measured by A) the need for antibiotics, B) seroma aspiration due to infection or C) surgical drainage.Cosmesis assessed by the patient at every planned outpatient clinic visit. At these visits patients are asked to rate the cosmesis of the chest wall using a numeric rating scale (NRS) on a scale from 0 to 10.Quality of life measured using the SF-12 (Short Form) Health Survey. This is a 12-item questionnaire used to assess health related quality of life from the patient’s perspective. Two subscales are derived from the SF-12: the Physical Component Summary (PCS) and the Mental Component Summary (MCS) with a range from 0 to 100. A score of less than 50 means the patient scores lower than the general population and a score of more than 50 means the patient scores higher than the general population. Patients will be asked at baseline and at every postoperative planned outpatient clinic visit to fill in this questionnaire.The number of outpatient department visits, measured during the first 6 months postoperatively. This will be measured to see if patients have to come to the hospital more often due to seroma or seroma related complications.Wound pain and pain at the drain site measured by the patient using the NRS on a scale from 0 to 10 at the first postoperative outpatient clinic visit.

All outcome measures will be measured during the first 6 months postoperatively.

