### Follow-up

The follow-up period will be 6 months after mastectomy. Patients will visit the outpatient department for evaluation at 1 week, 6 weeks, 3 months and 6 months. See Fig. 2 for the participant timeline. Table 1 represents the time schedule of enrolment, interventions and assessments.

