**ASSESSMENTS:**							
***Baseline characteristics***	X	X					
***Clinical assessment seroma and complications***				X	X	X	X
***Invasive interventions***			X	X	X	X	X
***SSI***				X	X	X	X
***Cosmesis***				X	X	X	X
***Additional OPD visits***				X	X	X	X
***Wound pain***				X			

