#### Secondary study parameter(s)

The proportion of patients with a surgical site infection will be compared between groups using Pearson’s chi-squared test. Differences in the mean scores on the SF-12 and the NRS for pain and for cosmesis will be compared using the independent-samples t-test. Poisson regression will be used to compare the number of outpatient department visits, measured during the first 6 months post-operatively. All secondary parameters will be tested on the intention to treat sample, and are measured over the first 6 months after treatment.

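### The outpatient-visit outcome is meant to show seroma-related attendance, but the count that is defined and tested is not limited by cause, so unrelated visits dilute the comparison

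*Protocol article*

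**What the plan says.** Under Secondary outcome measures, the protocol article defines the outcome as "The number of outpatient department visits, measured during the first 6 months postoperatively". The next sentence gives its purpose: "This will be measured to see if patients have to come to the hospital more often due to seroma or seroma related complications". The analysis, under Secondary study parameter(s), is: "Poisson regression will be used to compare the number of outpatient department visits, measured during the first 6 months post-operatively". It is run on the intention-to-treat sample.

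Three other places name the same outcome differently. The abstract has "number of additional outpatient department visits", Table 1 has "Additional OPD visits", and the secondary objectives ask whether patients "require more unplanned visits to the hospital".

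The planned schedule under Follow-up is the same in both arms: "Patients will visit the outpatient department for evaluation at 1 week, 6 weeks, 3 months and 6 months". For the drain arm, the article states: "Drain removal will be performed once daily output is below 50 mL or after a maximum of 48 h, irrespective of drain output". It does not say where removal takes place and schedules no outpatient drain visit.

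**The concern.** The purpose names a cause; the definition and the analysis do not. Nor do the alternative wordings: *additional* and *unplanned* exclude the four scheduled visits but leave in every unscheduled attendance, whatever its reason. The article limits by cause elsewhere. In the same section, invasive interventions count only if they relate to seroma or wound healing.

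The patients have invasive breast cancer or DCIS and are followed for six months after mastectomy, so some outpatient visits will probably have nothing to do with seroma. Counting them adds the same expected number to each arm, shrinks the ratio and adds variance. The trial could then report no clear difference in visits although seroma-related attendance differs, and the stated question would go unanswered. If no reason is recorded at the time, it may not be recoverable afterwards.

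**Working it through.** **Plan's own figure.** The article gives no expected visit rate and no power for this outcome. Its only sample size is for aspirations. With 10% in each group, a 10-point limit, 80% power and a one-sided 5% level (my assumption, since the level is not stated), n = (1.645 + 0.842)² × 2 × 0.10 × 0.90 / 0.10² ≈ 111.3, so 112 per group. Then 112 / 0.90 = 124.4, so 125. Both figures reproduce. They bear on this point only by fixing the number of patients.

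**Inputs.** From the article: 125 patients per arm and 4 planned visits per patient. Assumed: seroma-related visits per patient of 0.2 (drain) and 0.4 (no drain), or 0.3 and 0.5; unrelated visits of 0, 0.5 or 1 per patient, equal in both arms.

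**Formulas.** With λ0 and λ1 the total visits per patient counted in the drain and no-drain arms:

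- ratio = λ1 / λ0
- SE of the log ratio = √(1/(125 λ0) + 1/(125 λ1))
- power = Φ(|log ratio| / SE − 1.96)

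**Worked case, seroma visits only.** SE = √(1/25 + 1/50) = 0.245 and log 2 = 0.693, so 0.693/0.245 − 1.96 = 0.87 and power is 0.81.

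**With 0.5 unrelated visits.** The rates become 0.7 and 0.9. SE = √(1/87.5 + 1/112.5) = 0.143 and log 1.286 = 0.251, so 0.251/0.143 − 1.96 ≈ −0.20 and power is 0.42.

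| Visits added per patient, both arms | 0.2 v 0.4: ratio (power) | 0.3 v 0.5: ratio (power) |
|---|---|---|
| none | 2.00 (0.81) | 1.67 (0.70) |
| 0.5 unrelated | 0.9/0.7 = 1.29 (0.42) | 1.0/0.8 = 1.25 (0.38) |
| 1 unrelated | 1.4/1.2 = 1.17 (0.28) | 1.5/1.3 = 1.15 (0.27) |
| 4 planned, no unrelated | 4.4/4.2 = 1.05 (0.12) | 4.5/4.3 = 1.05 (0.11) |

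The last row shows why the wording matters. Read literally, the definition includes the four scheduled visits; the abstract, objectives and Table 1 do not.

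**Direction.** The effect is symmetric. If drain-free patients had fewer seroma visits (0.2 against 0.4), the ratio of 0.50 would move to 0.7/0.9 = 0.78 or 1.2/1.4 = 0.86, with the same loss of power.

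**Sensitivity to the count model.** Poisson variance is optimistic if visits cluster in a few patients. A simulation with overdispersed (negative-binomial) counts, 112 per group, a robust test at 5% and seroma visits of 0.4 against 0.8 gives 87% power for those visits alone. With 1, 2 or 4 unrelated visits per patient, power is 48%, 27% or 14%, and the ratio is 1.29, 1.17 or 1.09.

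**The case against.** The strongest reply is that a total count is a legitimate measure of burden, and a more objective one in an open trial, where staff who know the allocation would be judging why a patient came. The secondary objectives name no cause for unplanned visits. The case report forms are not shown and may already hold a reason for each visit. The trial is not sized for this outcome, so low power breaks no commitment. Most of this stands. It supports keeping the total count in view, and it means a missing data field cannot be asserted. It does not remove the mismatch: the article states both a cause-specific purpose and a count without one, and one of them has to change.

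A reader might go further and infer a bias in favour of drain-free surgery. Since the drain is out within 48 h and the first planned visit is at 1 week, any outpatient attendance for drain removal would be an additional visit in one arm only. The arithmetic can look striking. With 0.5 additional visits per patient in both arms and no seroma difference, outpatient removal in 10%, 25% or 50% of drain patients gives ratios of 0.83, 0.67 or 0.50, and in simulation (112 per group) a significant result in about 14%, 51% or 97% of trials. But the documents do not support the premise. No outpatient drain visit is described, and daily output recording with removal by 48 h fits in-hospital care at least as well. If all drains are removed in hospital, this effect is nil. If such visits did occur, they would be a real consequence of allocation to a drain and would belong in a total count.

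Nor do unrelated visits favour the drain-free arm. Randomisation balances them in expectation, and dilution works against whichever arm is truly better.

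**Conclusion.** The point holds in a limited form. As written, the definition and analysis answer a diluted version of the question the article sets, and its sections disagree on whether the planned visits count. Under the assumed rates, a seroma-visit ratio of 2.00 is seen as about 1.2 to 1.3 with 0.5 to 1 unrelated visit per patient, and power falls from 0.81 to between 0.28 and 0.42. These sizes rest entirely on assumed rates. If few unrelated visits occur and only additional visits are counted, the dilution is small.

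A one-arm distortion from drain care is conditional on outpatient drain removal or management, which the documents do not state, so it is not part of the conclusion. The outcome is secondary, and the non-inferiority conclusion on aspirations does not depend on it.

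**What to change.** 1. Use one wording, additional visits beyond the four planned, in the abstract, Secondary objectives, Secondary outcome measures, Table 1 and Secondary study parameter(s).
2. Record one reason for each additional visit: seroma or wound; drain care; other.
3. Compare the seroma/wound-related count between arms, which matches the stated purpose.
4. Report beside it the comparison of total additional visits, drain-care visits included, so that the burden of drainage is visible and the result does not rest on unblinded coding alone.

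The cost is one field on the case report form, if it is not already there, and a sentence in each of the sections named. The drawback is that the reason is assigned by staff who know the allocation; showing both counts lets the reader judge how much depends on it. If the sponsor wants only the total count, the purpose sentence should be rewritten to say so.

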## Abstract

**Background:**

Seroma formation is a common complication after breast cancer surgery and can lead to delayed wound healing, infection, patient discomfort and repeated visits to the outpatient clinic. Mastectomy combined with flap fixation is becoming standard practice and is currently combined with closed-suction drainage. There is evidence showing that closed-suction drainage may be insufficient in preventing seroma formation. There is reasonable doubt whether there is still place for closed-suction drainage after mastectomy when flap fixation is performed.

We hypothesize that mastectomy combined with flap fixation and closed suction drainage does not cause a significant lower incidence of seroma aspirations, when compared to mastectomy and flap fixation alone. Furthermore, we expect that patients without drainage will experience significantly less discomfort and comparable rates of surgical site infections.

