For many years closed suction drainage was considered the most effective intervention for reducing seroma formation after breast cancer surgery. This practice was supported by trials showing that mastectomy without the use of drains was associated with a higher occurrence of seroma and greater volumes of seroma in the post-operative period [19–23]. Other studies in drain free mastectomy have shown that application of suction drainage does not prevent seroma formation and that there is no significant difference between the incidence of seroma formation [24–26]. These studies also concluded that closed suction drainage is associated with a longer postoperative hospital stay on average, and that a long duration of drainage was related to a higher incidence of seroma formation [27–29]. The question therefore is if there is still a place for closed-suction drainage after mastectomy with flap fixation, as this has shown to decrease seroma formation [21, 22]. However, the evidence consists of only small case series and a large randomized controlled trial is needed to provide definitive proof.

To our knowledge, no randomized controlled trial has been conducted comparing flap fixation with and without the use of closed-suction drainage using seroma aspirations as the primary outcome. The SPIRIT Statement guidelines were used for designing and describing this trial [30, 31].

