## Objectives

### Research hypothesis

We hypothesize that flap fixation with closed suction drainage does not cause a significantly lower incidence of seroma aspirations when compared to flap fixation alone. We also expect that patients without drainage will experience less discomfort and will have comparable rates of surgical site infections.

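### The hypothesis of less discomfort without a drain is tested with no patient-reported score scheduled while any drain is in place

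*Protocol article*

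**What the plan says.** Under Research hypothesis the protocol article states "We also expect that patients without drainage will experience less discomfort". The abstract puts it more strongly: "we expect that patients without drainage will experience significantly less discomfort". Neither place defines discomfort or gives it a time window.

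In the drain arm (Mastectomy with low vacuum drainage), the drain is removed when daily output falls under a threshold or "after a maximum of 48 h, irrespective of drain output".

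Under Secondary outcome measures, wound pain is scored along with drain-site pain: "drain site measured by the patient using the NRS on a scale from 0 to 10 at the first postoperative outpatient clinic visit". Follow-up sets the visits: "Patients will visit the outpatient department for evaluation at 1 week, 6 weeks, 3 months and 6 months". Table 1 agrees, with a single mark for wound pain in the 1-week column. The table also has a Day 1 column, but its only mark is for invasive interventions. Data collection has pain reported at all four planned visits, the earliest of which is again 1 week. The SF-12 is completed at baseline and then at the planned outpatient visits. The secondary analysis compares NRS pain and SF-12 scores between arms by independent-samples t-test.

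**The concern.** The two arms differ physically for two days at most, and discomfort from having a drain would arise in those two days. The protocol names less discomfort as an expected gain from leaving the drain out, yet first asks patients about pain when nobody in either arm has a drain. If the 1-week comparison shows no difference, the trial cannot tell whether drains are not uncomfortable or whether the question came too late. What is at stake is the interpretation of one of the two further hypotheses that the protocol states beside its primary one. Scores not taken in the first two days cannot be recovered afterwards.

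**Working it through.** **Inputs**

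- Latest drain removal: 48 h (Mastectomy with low vacuum drainage).
- First pain score: first post-operative outpatient visit (Secondary outcome measures), which is at 1 week (Follow-up and Table 1).
- First post-operative SF-12: also the 1-week visit (Secondary outcome measures and Data collection).
- Evaluable patients: 112 per arm (Sample size).

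**Timing**

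1 week = 7 × 24 = 168 h. 168 − 48 = 120 h = 5 days.

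The gap is about 5 days for a drain kept to the limit, and longer for one removed earlier because of low output.

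**Does the answer depend on how the schedule is read?**

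| Source | When pain is asked | Earliest score |
|---|---|---|
| Secondary outcome measures | first outpatient visit | 1 week |
| Table 1 | one mark only | 1 week |
| Data collection | all four planned visits | 1 week |

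These places differ on whether pain is asked once or four times and should be reconciled. They agree on the earliest time, so the point holds under either reading.

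**The plan's own figure**

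The stated sample size concerns the primary outcome. With 10% aspirations in each arm, a 10-point margin and 80% power,

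n = (z₁₋α + z₀.₈₀)² × 2 × 0.10 × 0.90 / 0.10².

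A one-sided α of 0.05 gives 111.3, rounded up to 112; one-sided 0.025 gives 141.3, rounded up to 142. The stated 112 is therefore reproduced at one-sided 0.05 (the section states no α), and 112 / 0.90 = 124.4 rounds up to 125 per group. The timing point does not depend on this calculation, and the protocol makes no power claim for pain.

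**Illustration of what timing can cost**

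The documents give no effect size, SD or rate of decay for pain, so all three are assumed here. Suppose a drain adds 1 NRS point while in place and a fraction f of that difference remains when the question is asked. Power is that of a two-sided 5% two-sample t-test with n = 112 per arm and non-centrality f / (SD × √(2/112)).

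| Fraction f remaining | SD 2 | SD 2.5 | SD 3 |
|---|---|---|---|
| 1 (asked with drain in) | 96% | 85% | 70% |
| 0.5 | 46% | 32% | 24% |
| 0.25 | 15% | 12% | 10% |
| 0 | 5% | 5% | 5% |

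The table shows how strongly the test depends on f. It does not say which row applies to this trial.

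**The case against.** The best defence is that discomfort is not defined and is not limited to the time a drain is in place. The article also uses the word for the effects of seroma, both in its background and in the definition of clinically significant seroma. Its secondary objective on pain is open in direction. Wound pain, soreness where the drain was, and tension from seroma can all be present at 1 week, so a between-arm comparison then is legitimate. This stands.

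It rules out some stronger readings that a reader might infer:

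- That the relevant discomfort has ended by 1 week. The documents do not say so.
- That the 1-week comparison is biased. It estimates the 1-week difference without bias from its timing; what is open to question is whether that is the difference the hypothesis concerns.
- That the trial will probably fail to confirm its hypothesis. This would need the fraction remaining at 1 week, for which the documents give no figure.
- That omitting the drain can be justified only through the pain score. Infection, SF-12, cosmesis, invasive interventions and outpatient visits are outcomes too.
- That length of stay should be added to the point. The Background reports from earlier studies that "closed suction drainage is associated with a longer postoperative hospital stay on average", but the trial does not hypothesise a difference in stay.

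The pain question might also be put as recall since surgery. The article gives no recall period, and the wording of the form is not shown, so this neither rescues nor condemns the design.

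None of this supplies a score taken while a drain is in place. Nor is the gap a detail left to a fuller document: the article fixes the time of the pain score in the outcome definition and again in Table 1.

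**Conclusion.** The point holds in a limited form. No patient-reported measure is scheduled while the arms differ by the presence of a drain, and the first one comes about 5 days after the latest permitted removal. That follows from the document's own times and needs no assumption. A null result at 1 week would therefore leave the discomfort hypothesis unresolved as far as a drain in place is concerned. The 1-week score remains valid for later pain.

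How much sensitivity is lost cannot be determined from the document; the power figures are illustrative only. This is a worthwhile, inexpensive improvement to a secondary outcome. The primary test, the margin and the sample size are untouched.

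**What to change.** - Add one 0-10 rating of wound pain/discomfort at a fixed time on Day 1, worded identically in both arms. The Day 1 column already exists in Table 1. A drain-site question alone would not serve, as it has no counterpart in the arm without a drain.
- Record whether the drain is still in place when the rating is made.
- Name the Day 1 score as the test of the drain-discomfort hypothesis and keep the 1-week score as a separate, later outcome.
- While editing, reconcile Secondary outcome measures and Table 1 (pain at one visit) with Data collection (pain at all four).

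The cost is one extra rating per patient, one row or mark in Table 1 and one item on the case report form. No treatment or outpatient visit changes. The Day 1 score has limits that should be stated: it also reflects anaesthesia and analgesia, it is unblinded and so open to expectation effects, and it may miss drains already removed for low output. The change works only prospectively.

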### Follow-up

The follow-up period will be 6 months after mastectomy. Patients will visit the outpatient department for evaluation at 1 week, 6 weeks, 3 months and 6 months. See Fig. 2 for the participant timeline. Table 1 represents the time schedule of enrolment, interventions and assessments.

